## Abstract

**Background:**

At present, intraocular injection of anti-VEGF (vascular endothelial growth factor) drugs has replaced traditional laser therapy as the first-line treatment for DME (diabetic macular edema). However, ranibizumab, a commonly used anti-VEGF drug, is expensive and requires multiple intraocular injections. It places a heavy economic burden on patients with DME. Micropulse laser is safer than conventional laser and can reduce edema. Combined treatment with anti-VEGF may reduce the number of intraocular injections. This study will compare the efficacy of micropulse laser combined with ranibizumab treatment to ranibizumab monotherapy in the treatment of DME, providing a new regimen for future DME treatment.

**Methods:**

This study is a prospective randomized double-blind controlled clinical trial (RCT) in patients with DME. After 1-year follow-up, visual acuity and macular edema regression will be compared between micropulse laser combined with ranibizumab group and ranibizumab monotherapy group to determine whether the efficacy of micropulse laser combined with ranibizumab treatment was not lower than that of ranibizumab monotherapy in the treatment of DME. Visual acuity measured by the ETDRS chart is the primary outcome measure. The secondary outcome measures are CMT (central macular thickness) measured by OCT (optical coherence tomography) and the number of injections of two groups. Changes in visual acuity and CMT of the two groups will be compared at 12-month follow-up. Before patients are recruited, we provide them with informed consent, in which we explain to them the purpose and process of the study.

**Discussion:**

Micropulse laser combined with anti-VEGF drugs in the treatment of DME can reduce the number of intravitreal anti-VEGF injections, not only relieve the pain of the patients, but also ease the economic and psychological burden of patients, bringing great benefits. However, there is no treatment consensus for the parameters and specific methods of micropulse laser treatment for DME. There is a lack of clinical research data reference of micropulse laser combined with anti-VEGF therapy in clinical practice. This study intends to provide a new direction for clinical DME treatment and also provide a realistic consideration for the application of micropulse laser in DME treatment.

**Trial registration:**

ClinicalTrials.gov NCT03690947. Registered on 1 October 2018.

**Supplementary Information:**

The online version contains supplementary material available at 10.1186/s13063-022-06593-2.

## Administrative information

Note: the numbers in curly brackets in this protocol refer to SPIRIT checklist item numbers. The order of the items has been modified to group similar items (see http://www.equator-network.org/reporting-guidelines/spirit-2013-statement-defining-standard-protocol-items-for-clinical-trials/).

## Introduction

### Background and rationale {6a}

Diabetic retinopathy (DR) is one of the most common microvascular complications of diabetes, accounting for 13% of visual impairment in diabetic patients [1]. Diabetic macular edema (DME) is a common manifestation of DR and one of the major causes of visual loss in diabetic patients. There are many treatments for DME. Photocoagulation therapy, intravitreal anti-vascular endothelial growth factor (VEGF) injection, and intravitreal corticosteroid injection are its main methods [2]. The current first-line treatment for DME is an intravitreal injection of anti-VEGF agents [3], with ranibizumab being most commonly used in China. At present, the consensus of intravitreal ranibizumab injection is 3 consecutive monthly injections, followed by monthly follow-up and pro re nata (PRN) treatment. Several studies have shown that the number of injections within a year ranges from 7 to 8 [4]. Because ranibizumab is expensive and many DME patients suffer from recurrence, multiple intravitreal injections are needed, which brings a heavy economic and psychological burden to DME patients in China. Moreover, as the number of intravitreal injections increases, the risk of complications such as endophthalmitis also increases.

In previous studies of traditional macular grid photocoagulation combined with anti-VEGF therapy to treat DME, the timing of combined treatment was divided into immediate laser therapy and delayed laser therapy. Study results showed that combined treatment did not improve the visual acuity of patients or reduce the number of anti-VEGF injections and it left visible laser scars, causing damage to the retina, resulting in complications such as decreased visual acuity and reduced visual field. Therefore, the use of traditional photocoagulation is gradually decreasing. The 2017 European Union DME treatment guidelines stated that micropulse laser treatment is a promising treatment strategy for DME [5]. Micropulse laser is a type of subthreshold laser, which minimizes the damage of the neuroepithelial layer by reducing exposure time and energy. The guidelines stated that a micropulse diode laser emits a low-energy micropulse that confines the energy to the retinal pigment epithelium and avoids the outward spread of heat. Some randomized clinical studies have confirmed that the efficacy of micropulse diode laser treatment is comparable to that of traditional macular grid photocoagulation. However, it takes more time to achieve the same visual function and anatomical results [6, 7]. Therefore, guidelines recommended micropulse laser treatment for early diffuse DME patients with better visual acuity to avoid the spread of thermal energy and secondary chorioretinal injury. Compared to the previous diode micropulse laser, the new IQ577 nm micropulse laser has more obvious advantages. First, located in the inner and outer plexiform layers of the macula, lutein seldom absorbs yellow light. Therefore 577 nm yellow light is more suitable for the treatment of the macular than diode red light [8] with less damage. Second, treatment parameters such as duty cycle changed from 15 to 5% so that laser duration is shorter and the damage to the retina is less. Third, it is improved to a low-energy high-density grid laser with a better effect in eliminating edema. Previously, conventional lasers and other subthreshold lasers are forbidden within 500 μm diameter of the macula. But being able to treat in this range has become the most important innovation and advantage of the IQ577 nm micropulse laser. At present, some foreign studies and our own clinical experience have confirmed that 577 nm micropulse laser treatment for mild to moderate DME can effectively relieve edema and improve the visual function of patients [9]. The technique is simple and easy to learn, convenient for promotion, and more importantly, it can be easily accepted by patients for its cheap price.

To our knowledge, there were few prospective randomized controlled studies of micropulsed laser combined with anti-VEGF drugs in the treatment of DME. Only two retrospective studies published in 2017 and 2021 suggested that anti-VEGF drugs combined with the micropulse laser group could reduce the number of intravitreal injections compared to the anti-VEGF monotherapy group in the treatment of DME [10, 11].

### Objectives {7}

The purpose of this study is to evaluate the safety and efficacy of micropulse laser combined with intravitreal ranibizumab injections in the treatment of DME. Study subjects are 72 patients (more patients may be recruited) diagnosed with diabetic macular edema. By using a prospective randomized double-blind controlled study method, we hope to compare the changes of visual acuity and macular edema regression between micropulse laser combined with ranibizumab group with ranibizumab monotherapy group to determine whether the efficacy of micropulse laser combined treatment group in the treatment of DME is not lower than ranibizumab monotherapy and whether these two therapies are equally effective. Our goal is to reduce the number of intraocular injections and establish a new technique for the treatment of DME.

### Trial design {8}

This study is a prospective, single-center, randomized controlled, double-blinded non-inferiority clinical trial. A flow chart of the study design is shown in Fig. 1. Study subjects are 72 patients (more patients may be recruited) diagnosed with diabetic macular edema.

**Fig. 1 Fig1:**
[figure not shown]
A flow chart of the study design

#### Screening period: from day −14 to day −1

At screening (visit 1, between day −14 and day −1), after signing the informed consent (the model consent form is attached as a supplementary file), the patient is enrolled in the study and will undergo a series of examinations including ETDRS (Early Treatment Diabetic Retinopathy Study) visual acuity test, intraocular pressure measurement, slit-lamp, and indirect ophthalmoscopy, optical coherence tomography (OCT), optical coherence tomography angiography (OCTA), fundus fluorescein angiography (FFA), fundus color photography, vital signs, hematology, urinalysis, blood biochemistry, and glycosylated hemoglobin to assess eligibility for the study.

#### Treatment period: from day 1 to month 11

At baseline (visit 2, day 1), eligible patients will be randomized by 1:1 ratio into micropulse laser combined with ranibizumab group or ranibizumab monotherapy group. After baseline visit, all patients receive 3 consecutive monthly ranibizumab injections. Subjects will then return to the study site on day 90 (± 7 days) and according to the retreatment criteria, patients will either receive micropulse laser and sham intravitreal ranibizumab or sham micropulse laser and intravitreal ranibizumab. Thereafter, subjects will return to the study site every 30 days (± 7 days) for assessment (schedule shown in Fig. 2) and accept appropriate treatment according to the retreatment criteria.

**Fig. 2 Fig2:**
[figure not shown]
Assessment protocol from V1 to V14. *BSL *Base line, *EOT *End of treatment, *EOS *End of study. (X): Give treatment as needed. b: Except at the time of screening, at month 6 and at month 12 / end of the study, if the investigator needed information to evaluate the retreatment. These assessments are optional for therapeutic needs. c: Evaluation of both eyes. d: At 2 (±1) days after each study treatment, the investigator should contact the patient for a possible report of adverse events

Group I (micropulse laser combined with ranibizumab group): 3 consecutive injections of intravitreal ranibizumab, followed by monthly observation, if:A.Visual acuity decreases by greater than or equal to 5 ETDRS letters due to macular edema, then treat with micropulse laser therapy and sham intravitreal ranibizumab injection.B.Visual acuity stays stable for at least two consecutive treatments (3 consecutive changes of no more than 5 letters), discontinue micropulse laser treatment.

Group II (ranibizumab monotherapy group): 3 consecutive injections of intravitreal ranibizumab, followed by monthly observation. According to the investigator’s judgment, if:A.Visual acuity decreases by greater than or equal to 5 ETDRS letters due to macular edema, then treat with sham micropulse laser and intravitreal ranibizumab injection.B.Visual acuity stays stable for at least two consecutive treatments (3 consecutive changes of no more than 5 letters), discontinue intravitreal ranibizumab injection.

#### Post-treatment follow-up period: from month 11 to month 12

For all patients, the last study assessment will occur at month 12 (1 month after the last possible micropulse laser or intravitreal ranibizumab injection in the study).

## Methods: participants, interventions, and outcomes

### Study setting {9}

In this study, we will enroll 72 patients (more patients may be recruited) diagnosed with diabetic macular edema in the Department of Ophthalmology, Beijing Hospital. Patients are men or women aged 30 to 80 years who are able to give informed consent.

### Eligibility criteria {10}

#### Inclusion criteria

Patients must meet all of the following criteria to be eligible for enrollment in the study:Must sign an informed consent prior to performing any study-related assessments;Male or female aged 30 to 80 years;Diagnosed with type 2 diabetes, fasting blood glucose ≤ 10 mmol/L, glycosylated hemoglobin ≤ 10.0%;Diabetic medications must be fixed within 3 months prior to Visit 1 and are expected to remain unchanged during the study;Study eye must be diagnosed with non-proliferative diabetic retinopathy (NPDR), but not severe NPDR; the patient’s visual impairment was due to diabetic macular edema;Best corrected visual acuity (BCVA) ≥ 24 and ≤ 78 ETDRS letters in the study eye at screening and baseline;Presence of macular edema in the study eye shown on OCT examination with the central macular thickness (CMT) ≥300 um.The study eye had not been treated with macular grid photocoagulation, intraocular surgery, intravitreal injection of corticosteroids or anti-VEGF drugs within 3 months prior to baseline;BCVA ≥ 24 ETDRS letters of the fellow eye at screening;The fellow eye has not been treated with anti-VEGF drugs within 3 months prior to baseline.

If both eyes are eligible, the eye with worse vision at screening will be selected as the study eye. Only the study eye will be treated with ranibizumab and/or micropulse laser.

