### Sample size {14}

Using two-sided test, with αas 0.05, changes of visual acuity as less than 5 letters between two groups, standard deviation as 6.53 (REVEAL study [12] as reference), enrolling 56 cases of subjects can set the power to 90%. Considering drop out, set the lost follow-up rate as 20%, then the final sample size is calculated as 72 subjects, with 36 subjects in micropulse laser combined with ranibizumab group and 36 subjects in the ranibizumab monotherapy group.

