## Statistical methods

### Statistical methods for primary and secondary outcomes {20a}

The randomized set will consist of all randomized patients.

Full Analysis Set (FAS): Consists of all patients in the randomized set who are assigned to study treatment. They will be analyzed according to the treatment assigned to the subjects at randomization and the intention-to-treat principle.

Per Protocol Set (PPS): Consists of all patients in the full analysis set who complete the trial, had no significant protocol violations, and had no events that would confound the interpretation of the analysis. The analysis of the primary variable will be performed on the full analysis set.

For continuous and ordered categorical variables, analysis of variance (ANOVA) or analysis of covariance models which are both with baseline assessment as covariates were used to compare the changes between each treatment group and the baseline. Stratified and unstratified Cochran Mantel-Haenszel tests were also considered.

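### The 12-month BCVA model adjusts for the baseline reading only; adding the screening BCVA as a second covariate would be a small, unbiased gain in precision from data already collected

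*Protocol article*

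**What the plan says.** Protocol article, Inclusion criteria: study-eye BCVA must lie between 24 and 78 "ETDRS letters in the study eye at screening and baseline". Under Screening period, visit 1 falls between day −14 and day −1 and includes an "ETDRS (Early Treatment Diabetic Retinopathy Study) visual acuity test". Baseline is day 1, patients are randomised there, and the three ranibizumab injections follow that visit. Both readings therefore precede treatment.

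Statistical methods {20a}: change from baseline is compared by ANOVA or ANCOVA models, "which are both with baseline assessment as covariates". The Primary outcome measure section speaks of BCVA at baseline and at follow-up visits. Screening BCVA is used for eligibility and, if both eyes qualify, for choosing the worse eye. No analysis use is stated.

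Sample size {14}: two-sided 5% test, "changes of visual acuity as less than 5 letters between two groups", SD 6.53, 90% power with 56 subjects, and 72 after a 20% allowance for loss.

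**The concern.** A single acuity reading carries measurement error. As a covariate it predicts month-12 BCVA less well than two readings would. The second reading already exists, and treatment cannot have affected it. In a small non-inferiority trial the width of the confidence interval matters, so leaving it out of the model gives up precision that would cost no extra visit. Precision is all that is at stake; bias is not.

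**Working it through.** **1. The plan's own power figure.** Inputs from Sample size {14}: difference 5, SD 6.53, two-sided 0.05, 56 evaluable (28 per arm).

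- n per arm for 90% power = 2 × (6.53 × (1.960 + 1.282) / 5)² ≈ 35.8, so 36 per arm.
- Standard error at 28 per arm = 6.53 × √(2/28) = 1.745. Then 5/1.745 − 1.960 = 0.905, which is 81.7% power (80.3% by the t-test).

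The stated 90% is not reproduced. That is a separate sample-size matter, but it sets the starting point here.

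**2. Model for the gain.** Let T be true baseline BCVA, B0 = T + e0 the screening reading, B1 = T + e1 the day-1 reading, and Y = sT + d + e2 the month-12 reading. Each error has variance e². Var(Y − B1) is held at 6.53² = 42.64, so var(d) = 42.64 − (1 − s)²·var(T) − 2e².

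Assumed, because the article gives none of them: e = 2 to 4 letters, SD(T) = 9 to 14, s = 0.8 to 1.0. Taking 6.53 as the SD of change is also an assumption.

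- Residual variance = s²·var(T)·v/(var(T) + v) + var(d) + e².
- v = e² with day-1 BCVA alone; v = e²/2 with both readings as separate covariates.

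Worked case, s = 1, SD(T) = 12, e = 3: var(d) = 42.64 − 18 = 24.64.

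- One reading: 144·9/153 + 24.64 + 9 = 42.11.
- Two readings: 144·4.5/148.5 + 24.64 + 9 = 38.00, a fall of 9.8%.

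**3. Cost of one degree of freedom.** With N = 56 and k covariates, the variance of the treatment contrast is inflated on average by 1 + k/(N − k − 3). From one covariate to two, the ratio is (1 + 2/51)/(1 + 1/52) = 1.0196. In the worked case the net fall is 1 − 38.00 × 1.0196/42.11 = 8.0%.

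For s = 1 and SD(T) = 12:

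| e (letters) | One reading | Two readings | Fall | Net fall |
|---|---|---|---|---|
| 2 | 42.53 | 40.61 | 4.5% | 2.6% |
| 3 | 42.11 | 38.00 | 9.8% | 8.0% |
| 4 | 41.04 | 34.22 | 16.6% | 15.0% |

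Over SD(T) 9, 12, 14 and slopes 0.8 and 1.0, the fall is about 3-17% and the net fall about 1-15%. At slope 1, t-test power for 5 letters at 28 per arm goes from about 80-82% to about 81-87% after the cost.

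**4. If screening is noisier than day 1.** Give B0 an extra error SD of x letters and weight the readings optimally: v = 1/(1/e² + 1/(e² + x²)). With e = 2, x = 3, s = 1, SD(T) = 12: v = 1/(1/4 + 1/13) = 3.06 and the residual is 144·3.06/147.06 + 34.64 + 4 = 41.64. That is a fall of 2.1%, and 0.2% net. At slope 0.8 the net figure is about zero or slightly negative.

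**5. Using the mean of the two readings instead.** If change is still taken from B1, the half-difference (B1 − B0)/2, with variance e²/2, sits in the outcome but is independent of the mean. The residual is therefore the two-reading value plus e²/2.

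- s = 1, SD(T) = 12: 40.61 + 2 = 42.61, 38.00 + 4.5 = 42.50 and 34.22 + 8 = 42.22.
- Against one reading (42.53, 42.11, 41.04) this is 0.2%, 0.9% and 2.9% worse.
- At slope 0.8 it is about 2-13% worse.

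**6. Cross-check by correlations.** With ρ the correlation of one reading with month 12 and r the test-retest correlation, the relative fall is ρ²(1 − r)/[(1 + r)(1 − ρ²)]. It is 3.0% at ρ = 0.6, r = 0.9 and 17.0% at ρ = 0.7, r = 0.7. Over ρ 0.4-0.8 and r 0.7-0.95 it runs from 0.5% to 31%.

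**The case against.** The strongest reply is that nothing here is wrong. ANCOVA on one baseline value is valid, and the article does not define the baseline assessment; an analysis plan that is not shown may do so. That stands, and it limits the point to an optional improvement. Reading the term as the day-1 value is natural, since visit 2 is called baseline, but it remains a reading.

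Second, the size rests wholly on assumed inputs. That also stands. The upper end is demanding: at e = 4, 2e² = 32 of 42.64, so 75% of the variance of 12-month change would be measurement noise.

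Third, the two readings may not be exchangeable. Screening BCVA selects the worse eye when both qualify, so it may carry regression to the mean, and both readings are restricted to 24-78 letters. This can shrink the gain. It is a reason to enter the readings separately, so that the data set their weights.

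Fourth, the gain is smaller still if month-3 BCVA is also in the model. That is correct.

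A reader might infer that the primary comparison is biased or incorrectly specified, or that 3-17% is an established loss. The documents support neither: both readings precede treatment, adjustment for one is unbiased, and no measurement error or correlation is reported.

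**Conclusion.** The point holds as a small missed gain in precision. Two pre-treatment BCVA readings exist, the model names only the baseline one, and adding the other cannot bias the comparison. The reduction in residual variance is about 3-17% before and about 1-15% after the degree-of-freedom cost at 28 per arm, under the assumed error, spread and slope. It is about zero if error is near 2 letters and screening is noisier than day 1.

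A reader might also infer that this repairs the sample-size shortfall. It does not: at slope 1, power reaches 81-87% against the stated 90%. At slope 0.8 with SD(T) = 12, the same model already gives 87-92% with one reading, so power there depends mainly on the assumed slope and not on the second covariate.

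**What to change.** Keep day-1 BCVA in the primary ANCOVA and add screening study-eye BCVA as a second, separate covariate, with the outcome left as change from day 1 at month 12. State this in writing before unblinding. Do not substitute the mean of the two readings as the covariate while change is taken from day 1.

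The cost is one line of analysis wording and one degree of freedom; no visit or measurement is added. The same could be done for CMT, since OCT is also performed at screening, but that is optional and its benefit has not been quantified.

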#### Exclusion criteria

Patients who meet any of the following criteria are not eligible for inclusion in the study:Inability to follow study or follow-up procedures;Pregnant or lactating women and women with reproductive ability not taking effective contraceptive measures;History of stroke or myocardial infarction within 3 months prior to screening;Renal failure or creatinine level > 2.0 mg/dl;Uncontrolled systemic diseases and treatments that may affect the study results;Active ocular infection or intraocular inflammation in any eye;Iris neovascularization or neovascular glaucoma in any eye;History of uveitis or vitreomacular traction in any eye;Glaucoma or intraocular pressure (IOP) ≥ 24 mmHg in the study eye.

### Who will take informed consent? {26a}

Potential trial participants will be provided with an informed consent drafted by the primary investigator in a reception room. A sub-investigator will explain the purpose and process of the study in detail. After fully understanding their rights and obligations, risk and benefits, potential trial participants, or authorized surrogates will sign two identical informed consent forms. One will be kept by the study group, the other one will be kept by the participant.

### Additional consent provisions for collection and use of participant data and biological specimens {26b}

Not applicable, there are no additional consent provisions, and this trial does not involve collecting biological specimens for storage for use in the current study.

## Interventions

### Explanation for the choice of comparators {6b}

We used BCVA and CMT as the main outcome measures. BCVA is a functional indicator and effective treatment is to improve or maintain patients’ vision. CMT is often reduced before visual acuity improvement and could be used as a morphological indicator.

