#### Secondary outcome measures

CMT: OCT is used to measure CMT at baseline and every follow-up visit. Changes of CMT will be compared between the two groups at 12-month follow-up.

Number of injections: Number of intravitreal injections of two groups will be compared at a 12-month follow-up.

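### The primary BCVA model does not name baseline CMT as a covariate, although every study eye has it: adding it is an optional, nearly free gain in precision

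*Protocol article*

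**What the plan says.** The relevant text is in four places in the protocol article.

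- **Explanation for the choice of comparators {6b}** gives the reasons for using BCVA and CMT as outcomes, and says that "CMT is often reduced before visual acuity improvement and could be used as a morphological indicator".
- **Inclusion criteria** require "Presence of macular edema in the study eye shown on OCT examination with the central macular thickness (CMT) ≥300 um". That is a floor with no stated ceiling. They also require that the visual impairment be caused by the macular edema.
- **Secondary outcome measures** state that "OCT is used to measure CMT at baseline and every follow-up visit", so each study eye has a pre-treatment value.
- **Statistical methods {20a}** gives one general rule for continuous and ordered outcomes, an ANOVA or "analysis of covariance models which are both with baseline assessment as covariates were used to compare the changes" from baseline. It names neither BCVA nor CMT. The usual reading is that each outcome is adjusted for its own baseline, so baseline BCVA enters the primary analysis.

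Two further sections bear on the point. Sequence generation {16a} describes a single unstratified list of 72. Methods for additional analyses {20b} stratifies by DME type (focal or diffuse) and by baseline BCVA, not by CMT.

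**The concern.** All eligible eyes have lost vision through macular edema, and the amount of edema at entry is recorded before treatment. If starting thickness explains some of the variation in 12-month BCVA change that baseline BCVA does not, a model without it leaves that variation in the residual. The confidence interval for the arm difference is then wider than it needs to be.

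Precision matters here. The trial is small, its conclusion is one of non-inferiority, and the Trial status section reports patients lost to follow-up. A covariate already in hand is one of the few ways to gain information without more patients or visits.

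**Working it through.** **Inputs from the Sample size section {14}**

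- Test: "Using two-sided test, with αas 0.05".
- Difference: 5 letters, from "changes of visual acuity as less than 5 letters between two groups".
- Spread: "standard deviation as 6.53".
- Claim: "enrolling 56 cases of subjects can set the power to 90" per cent, so 28 evaluable per arm; 36 per arm are enrolled.

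**Step 1. The plan's own figure**

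Patients per arm for 90% power, normal approximation:

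2 × 6.53² × (1.960 + 1.282)² / 5² = 35.8, so 36 per arm, or 72 evaluable.

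The stated 56 is not reproduced. With 28 per arm the standard error is 6.53 × √(2/28) = 1.745 and the noncentrality is 5 / 1.745 = 2.865. Power is 81.7% by the normal approximation and 80.3% by the noncentral t. This shortfall is a separate matter. It is shown here because the comparison below has to start from about 80%, not 90%.

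**Step 2. Effect of adding baseline CMT**

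Let r be the partial correlation of baseline CMT with month-12 BCVA change, given baseline BCVA. The documents give no value, so 0.1 to 0.4 is an assumption, with 0 as the no-benefit case. Take 6.53 as the residual SD before CMT is added. Then:

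- residual SD with CMT = 6.53 × √(1 − r²);
- power from the noncentral t at 28 per arm, with 53 degrees of freedom for one covariate and 52 for two;
- equivalent extra evaluable patients = 56 × (1/(1 − r²) − 1).

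| Model | Residual SD | Variance removed | Power | Equivalent extra patients |
|---|---|---|---|---|
| Baseline BCVA only | 6.53 | – | 80.31% | – |
| + CMT, r = 0 | 6.53 | 0% | 80.28% | 0 |
| + CMT, r = 0.1 | 6.50 | 1% | 80.7% | 0.6 |
| + CMT, r = 0.2 | 6.40 | 4% | 81.9% | 2.3 |
| + CMT, r = 0.3 | 6.23 | 9% | 83.8% | 5.5 |
| + CMT, r = 0.4 | 5.98 | 16% | 86.6% | 10.7 |

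The normal approximation gives the same pattern about 1.2 to 1.4 points higher: 81.7% without CMT, then 82.1%, 83.3%, 85.2% and 87.8% for r = 0.1 to 0.4.

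**Step 3. Is chance imbalance a separate problem?**

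At 36 per arm the difference in mean baseline CMT, in units of its SD, has standard deviation √(2/36) = 0.236. An imbalance of that size moves the estimated BCVA difference by 0.236 × r × 6.53, which is 0.15 letters at r = 0.1 and 0.62 letters at r = 0.4. These movements are part of the sampling error that the interval already covers. In simulation with 36 per arm, the test without CMT kept its two-sided type I error at 4.9% (r = 0.3) and 5.0% (r = 0.5). This is the precision loss of Step 2 seen from another side, and it should not be counted twice.

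**The case against.** The case against raising this at all is a fair one, and most of it stands.

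- *The article may simply not list the covariates.* The wording on covariates is unspecific, and a fuller list could sit in an analysis plan that is not shown. A reader might infer that the protocol excludes baseline CMT from the primary model. The text does not support that; it is silent on CMT.
- *The remark on CMT is about something else.* It concerns the order in which two outcomes respond to treatment. A reader might infer that the protocol itself treats baseline CMT as prognostic for 12-month BCVA. No section says so. The baseline value also precedes three injections given to everyone, and the arms diverge only at about day 90. The requirement that visual impairment be due to edema makes a link plausible, but gives no correlation beyond baseline BCVA.
- *Chance imbalance is not a defect.* A reader might infer that unstratified allocation of 72 patients leaves the BCVA comparison biased by edema severity. Randomisation and the simulated error rates above rule that out.
- *The size is assumed.* For r of 0.2 or less the gain is at most 1.6 points of power. Nor does the sample size section say whether 6.53 is already adjusted for baseline BCVA.

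What survives is narrow. The protocol does state a covariate rule, that rule on its natural reading does not use a measurement the trial already holds, and using it costs almost nothing.

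**Conclusion.** The planned analysis is valid as written. The point is an optional refinement: baseline CMT is available in every study eye and is not named in the primary BCVA model. Under an assumed partial correlation of 0.1 to 0.4 beyond baseline BCVA, with 6.53 letters as the SD before CMT adjustment and 28 evaluable per arm, adding it raises power by 0.4 to 6.3 percentage points, from 80.3% to between 80.7% and 86.6%. If CMT adds no information, power falls by about 0.03 points. The benefit is negligible in the lower half of that range and useful only towards its top, and the documents do not show where the true value lies. It is low priority and worth doing because the possible loss is so small.

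**What to change.** Before unblinding, state the primary model in the analysis section: ANCOVA of month-12 change in BCVA on treatment, baseline BCVA and baseline CMT of the study eye, with both baseline values continuous and not cut into categories. Take the confidence limit for the arm difference from that model. Keep the ANCOVA with baseline BCVA alone as a prespecified sensitivity analysis. If an existing analysis plan already lists the covariates, check whether CMT is among them and make the change there.

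The same sentence would settle the open choice between ANOVA and ANCOVA for the primary outcome. The cost is one sentence and one degree of freedom, with no new data, visits or patients.
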